### Additional outcomes

#### Anthropometry

Height and weight of the women were measured at baseline, and weight was monitored at each sample collection time point. Height was measured using a height board. The participant was to stand still with her back towards the scale, with the heels, back of the calves, upper back and the back of their head touching the board with the scale. The head was positioned so that the Frankfurt line was straight. The measuring device was lowered gently on the hair until it rested gently on the scalp. For the measurement of weight, women were asked to relax for 5 min before being asked to remove added clothes, shoes, socks, anything in the pocket, watch or necklace. The woman was asked to stand on the marked position on the scale until the digital reading or the reading needle stabilised. For consistency, weight was measured three times and the average calculated. In addition, the height and weight of at least one child under 10 years in each household will be monitored throughout the intervention period. Mothers were also be asked to keep a diary of the frequency and duration of diarrhoeal episodes of children in the household throughout the intervention period.

#### Haematological and micronutrient analyses

Haematocrit, haemoglobin, mean corpuscular volume, total iron binding capacity and transferrin saturation will be estimated using clinical haematology methods. Blood samples will be analysed for micronutrient status including serum transferrin receptor and ferritin (sandwich ELISA), Fe and SE concentrations (ICP-MS), vitamin A (retinol-binding protein, RBP) and inflammatory markers (α1-acid glycoprotein and CRP).

#### Dark adaptation

The potential impact of increasing dietary Zn intake on dark adaptation was measured at baseline, week 2, week 10 and week 18 during the participants’ visits to the health centre. Dark adaptation was measured using a novel device developed by Labrique and coworkers.^24^

#### Stool samples for parasite infection and microbiome analysis

Stools were collected at baseline, week 2, week 10 and week 18. Samples were analysed within 24 hours for presence of parasites. Samples were stored to create a biobank for future short-chain fatty acid and microbiome analysis.

## Data collection and storage

Sample analysis will take place in a number of different specialist laboratories in the UK (University of Nottingham: plasma Zn, Fe and SE, water, flour), USA (NeurobioTex: nail and hair Zn concentration) and Pakistan (KMU: Comet assay, haematology, serum transferring receptor, ferritin, RBP and inflammatory markers). Comet assay tail-moment analysis will be undertaken by both Pakistan-based (KMU) and UK-based (University of Central Lancashire, UCLan) teams, and the results compared. Any significant differences will be resolved with expert support from the Children’s Hospital Oakland Research Institute. Sample analysis will be undertaken in duplicate as a minimum requirement. Data entry will be undertaken by the expert laboratory and encrypted spreadsheets sent to the data hub where a final check for anomalies will be made by the database manager. Any potential anomalies identified will be checked with the expert laboratory. All data will be managed compliant with standard BBSRC policies (http://www.bbsrc.ac.uk/web/FILES/Policies/data-sharing-policy.pdf). The UCLan will be the data hub for the project; UCLan adheres to an Open Data policy and has an open data repository. Metadata will be collected in the form of ‘read me’ files using basic Dublin Core. This study will generate small quantities of personal data from the analysis of blood and hair/nail samples. Most of the participants were illiterate so verbal informed consent was obtained and recorded by the project manager. Participants were given an ID number on recruitment, and this will be used in all data files. The list of names associated with the ID numbers is known only by the project manager and is stored in a locked filing cabinet. Data collected in the field on laptops are password protected. UCLan systems are automatically backed up. Transfer of data between laboratories will be in the form of encrypted Excel or Word files. Data and metadata will be securely stored in a project database and reported on publication. Data will be shared with the project steering committee during the bi-monthly meetings. This committee is composed of the PI and Co-Is. The database manager is undertaking the role of data monitoring and all members will have access to the final database.

## Statistical analysis plan

The analysis will be performed as intention to treat. Descriptive statistics will summarise participants’ characteristics and outcome measurements at each time point, using methods appropriate for the type of data. Most study outcome measurements will be quantitative data. The primary outcome, plasma Zn concentration, was collected at five time points (baseline, weeks 4, 8, 12 and 16). After adjustment for inflammatory markers and as described above, the primary outcome will be assessed in two type comparisons:

### Within-group (A and B) comparisons

Within each group of participants, the study outcome will be compared at appropriate time points (baseline will be compared with week 4 and week 8, week 4 compared with week 8, week 12 with week 16) to assess trend of the change (increase or decrease) in Zn concentrations. The pairwise comparisons will be done using paired t-test or Wilcoxon signed-rank test if normality assumptions for t-test are not satisfied. Repeated-measures ANOVA (or its non-parametric analogue) will be applied for comparisons at multiple time points (eg, to compare study outcome at baseline, week 4 and week 8).

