The intervention trial was composed of a 2-week baseline equilibration period and two 8-week intervention/control periods. The baseline period started on 1 October 2017. During the baseline period, all the participating households were provided with control flour. After 2 weeks, group A received biofortified flour and group B received control flour. After 8 weeks, the two groups will cross over, with group A receiving control flour and group B receiving biofortified flour for the final 8 weeks (figure 1). Freshly milled flour was provided on a fortnightly basis for consumption by the entire household (average seven individuals, including children). Families will be asked not to consume any other flour within the household during the 18-week study period. Compliance was monitored at each flour distribution time point through interview with the head of the household. The number of meals consumed outside the household by the primary study participant (woman of childbearing age) was recorded. Our previous knowledge of this community indicates that, other than community events such as weddings, it is unusual for women to eat outside the home.

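### No listed pairwise test uses the within-woman cross-over contrast: the within-group pairs never compare flours in group B, and in group A only against the earlier baseline

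*Protocol article*

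**What the plan says.** Under Study design, both groups start on the same flour: "During the baseline period, all the participating households were provided with control flour". Then "After 2 weeks, group A received biofortified flour and group B received control flour", and after 8 weeks they swap, "with group A receiving control flour and group B receiving biofortified flour for the final 8 weeks". Plasma zinc is sampled at baseline and at weeks 4, 8, 12 and 16.

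The Statistical analysis plan section announces two types of comparison for the primary outcome. The first is within group, with the pairs "baseline will be compared with week 4 and week 8, week 4 compared with week 8, week 12 with week 16", by paired t-test or Wilcoxon signed-rank test. The stated aim is "to assess trend of the change (increase or decrease) in Zn concentrations". "Repeated-measures ANOVA (or its non-parametric analogue) will be applied for comparisons at multiple time points", with baseline, week 4 and week 8 as the example.

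The second type, under Comparisons between groups A and B, is assigned the primary research question. It compares A with B at weeks 8 and 16, with weeks 4 and 12 as a complement, by unpaired t-test or Mann-Whitney test. A linear mixed model is added for adjusted analyses that take in baseline, repeated measurements and covariates. No flour, period or sequence term is named.

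The Strengths and limitations list concedes that 50 is a small sample and offers the cross-over design, through its gain in power, as the remedy.

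**The concern.** A cross-over gains power because each woman eats both flours and serves as her own control. To use that gain, an analysis must set a woman's period 1 value against her period 2 value. The within-group list is where a reader would look for that pair, and it stops at the period boundary on both sides. The between-group tests compare different women at one visit, which is a parallel-group analysis done twice.

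Two things are at stake. First, a significant baseline-to-week-8 rise in group A could be reported as a flour effect when it may partly reflect time: the 2-week baseline began on 1 October 2017, so week 8 of the intervention falls around 10 December. Second, if the pairwise tests are the main analysis, the precision used to justify the sample size is not delivered.

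**Working it through.** **1. Flour map.** Inputs: Study design (flour by period), Statistical analysis plan (visits), Within-group comparisons (pairs). C = control, Z = biofortified.

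| Pair | Group A | Group B |
|---|---|---|
| baseline, week 4 | C, Z: differ | C, C: same |
| baseline, week 8 | C, Z: differ | C, C: same |
| week 4, week 8 | Z, Z: same | C, C: same |
| week 12, week 16 | C, C: same | Z, Z: same |
| week 8, week 16 (not listed) | Z, C: differ | C, Z: differ |

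Flours differ in 2 of 4 listed pairs in A and 0 of 4 in B. No listed pair links the two periods. The map is the same whether weeks are counted from the start of the baseline period or from the start of period 1, and it needs no assumption about variability.

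**2. What each contrast estimates.** Let f be the flour effect and p0, p1, p2 the time levels at baseline, week 8 and week 16.

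- Group A, week 8 minus baseline: f + (p1 − p0). A common time shift enters in full.
- Group A, week 8 minus week 16: f + (p1 − p2).
- Group B, week 8 minus week 16: −f + (p1 − p2).
- Half the difference of the last two: f. A common period shift cancels.
- If a residue c of biofortified flour persists at week 16 in group A, that half-difference becomes f − c/2. The week 8 comparison of A with B contains no c.

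**3. The plan's own figures** (Study setting and recruitment). Attrition: 40/(1 − 0.20) = 50, which reproduces. The 40 itself cannot be reproduced because neither an SD nor a within-woman correlation is given. It can only be solved backwards, with 1.960 + 1.282 = 3.242 for two-sided 5% and 90% power:

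- Paired reading: SD of differences = 3.1 × √40 / 3.242 = 6.05 µg/dL.
- Parallel reading, 20 per group: SD = 3.1 / (3.242 × √(2/20)) = 3.02 µg/dL.

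**4. Precision, if the paired reading was meant (assumption).** The between-woman SD is 6.05/√(2(1 − ρ)), where ρ is the within-woman correlation. Power of the unpaired test, 20 against 20, for 3.1 µg/dL:

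| ρ | SD (µg/dL) | Power |
|---|---|---|
| 0 | 4.28 | 63% |
| 0.3 | 5.11 | 48% |
| 0.5 | 6.05 | 37% |
| 0.7 | 7.81 | 24% |

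The two-sequence week 8/week 16 contrast with 20 + 20 women has SE = (6.05/2) × √(2/20) = 0.956 and power 90%, the stated value. Under the parallel reading the unpaired test has the stated 90% by construction; the cross-over then plays no part in the sample size.

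**5. Time shift in group A (illustrative assumption).** With SD of differences 6.05, n = 20 (SE 6.05/√20 = 1.35), a normal approximation and no flour effect, the baseline-to-week-8 paired test rejects in 5%, 11%, 32% and 63% of trials for a shift of 0, 1, 2 and 3.1 µg/dL. The documents give no shift; these values only show sensitivity.

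**The case against.** The strongest reply is that the within-group tests are not meant to answer the flour question. Their stated purpose is trend, and for that same-flour pairs are useful: weeks 4 to 8 and 12 to 16 show whether zinc has levelled off, and group B's control-flour series in period 1 shows the drift that could disturb group A. The primary question goes to concurrent randomised comparisons, where a common time shift cancels. All of this stands.

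A reader might therefore go too far in three ways.

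- One might infer that the plan has no within-woman evidence at all, or that its primary inference is confounded with time. The documents do not support either. The mixed model for repeated measurements could supply the contrast, and a condensed article may leave its terms to a fuller plan. As an estimate the contrast is not even lost: with complete data, (A8 − A16) − (B8 − B16) = (A8 − B8) − (A16 − B16), which combines two comparisons already listed. What the unpaired tests lose is precision.
- One might infer that paired tests and repeated-measures ANOVA contradict "The analysis will be performed as intention to treat" because they need complete samples. They do not: intention to treat means analysing women as randomised. The recruitment target already allows for the planned attrition.
- One might treat a particular drift as established. None is documented, and infection is partly handled by adjusting plasma zinc for inflammatory markers.

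It is also fair that the week 8/week 16 contrast is open to carry-over, because the article describes a direct switch of flours. That limits the remedy, not the observation.

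What remains is that the article does fix the list of pairs, does count it as one of two assessments of the primary outcome, and does rely on the cross-over for power.

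**Conclusion.** The point holds for the listed pairwise tests. None contrasts the flours in group B, two do so in group A but only against an earlier date, and none links period 1 with period 2. This follows from the schedule alone.

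The consequence for the primary question is inefficiency, not invalidity. Its size depends on what the 40 meant: power of 24% to 63% instead of 90% for the single-visit unpaired test if the calculation was paired and the correlation lies between 0.7 and 0, and no shortfall against the stated power if it was a parallel-group calculation with SD 3.02 µg/dL. The risk of misreading group A's before-after change is real, but its size is unknown. The change is worth making before unblinded analysis; the randomised comparisons do not depend on it.

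**What to change.** - State as the main flour-effect analysis the flour term of the linear mixed model already planned, with period and sequence terms and woman as a random effect, fitted to all observed samples. For complete end-of-period data this amounts to week 8 minus week 16 compared between sequences. If the mid-period samples are included, let the flour effect differ between mid and end of period so that the end-of-period effect can be reported.
- Keep the week 8 comparison of A with B as a supporting check, since it is free of carry-over.
- Label the within-group time courses, including the repeated-measures ANOVA, as descriptive of trend and not as evidence of a flour effect.

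The cost is wording only: the samples and the modelling are already in the plan. The downside is that the pooled contrast assumes that carry-over into weeks 12 to 16 is small, and this should be stated beside the result.

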### Comparisons between groups A and B

To answer the primary research question of determining the effectiveness of consuming flour made from agronomically biofortified wheat for improving Zn status, study outcomes will be compared between groups A and B at week 8 and week 16, complemented with comparisons at interim collection points, week 4 and week 12. The pairwise comparisons will be done using independent-samples t-test or Mann-Whitney U test as appropriate. Linear mixed modelling will be used for adjusted analyses to account for the baseline, repeated measurements and relevant covariates. Similar analysis will be done for all secondary outcomes measuring Zn status.

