**Registration details:**

The trial has been registered with the ISRCTN registry, study ID ISRCTN83678069.

Strengths and limitations of the studyThe study is the first randomised controlled trial to determine the effectiveness of consuming flour from the Zincol-2016/NR-421 strain of wheat on Zn status in women of childbearing age.The study will evaluate the use of novel biomarkers of Zn status in low-resource settings.A limitation of this study is the relatively small sample size (n=50). This is compensated for by the cross-over design, which strengthens the statistical power.

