Ten households from each cluster were randomly selected. The head of the household was approached, the purpose of the study explained and, if eligible, the family invited to participate in the trial. If the head of the household declined, another house from the cluster was randomly selected and the invitation process repeated. Inclusion criteria were the household included a woman aged 16–49 years who was neither pregnant nor breastfeeding, and not currently consuming nutritional supplements. When there was more than one eligible woman in the household, one was conveniently selected with agreement from the head of the household. There were no additional exclusion criteria. Following informed consent, each household was assigned to treatment arm A or B (refer to figure 1) using a block design. A sample size of 40, 95% significance level (two-sided) and 90% power, will enable an increase in plasma Zn concentration of 3.1 µg/dL to be detected. The target was to recruit 50 households (50 eligible women) to be able to accommodate a 20% attrition rate during the 18-week study. The project manager led the recruitment process because he is known to the community through previous health-related projects associated with the Abaseen Foundation PK (AFPK), a local non-governmental organisation and key member of this project team, along with its sister organisation Abaseen Foundation UK. There is a high level of trust and cooperation between community members and the AFPK who operate the health centre that serves this Union Council; therefore, high levels of participant enrolment has been achieved. The project manager was responsible for allocating participants to each arm of the cross-over trial using a block design. Only the project manager had access to this information.

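### The tests named for the primary question compare groups A and B separately at weeks 8 and 16, do not use the within-woman contrast, and come with no rule for which result decides

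*Protocol article*

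**What the plan says.** The section on comparisons between groups A and B introduces the analysis that is to answer the primary research question: "study outcomes will be compared between groups A and B at week 8 and week 16, complemented with comparisons at interim collection points". The method follows: "The pairwise comparisons will be done using independent-samples t-test or Mann-Whitney U test as appropriate". The next sentence adds a model: "Linear mixed modelling will be used for adjusted analyses to account for the baseline, repeated measurements and relevant covariates".

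The within-group section lists paired comparisons of baseline with weeks 4 and 8, week 4 with week 8, and week 12 with week 16. Week 8 against week 16 is not among them.

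The study design section describes a direct switch: "After 8 weeks, the two groups will cross over, with group A receiving control flour and group B receiving biofortified flour". No washout is mentioned.

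The strengths and limitations list concedes that n=50 is small and says: "This is compensated for by the cross-over design, which strengthens the statistical power". The sample-size statement, under study setting and recruitment, reads "A sample size of 40, 95% significance level (two-sided) and 90% power", and this "will enable an increase in plasma Zn concentration of 3.1 µg/dL to be detected". It gives no SD, no within-woman correlation, and no indication whether the calculation was paired or two-group.

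**The concern.** Every woman eats both flours, so the efficient estimate of the flour effect compares her zinc at the end of one period with her zinc at the end of the other. No named test makes that comparison. The between-group tests treat each week as a parallel-group trial. The listed paired tests either start from baseline or stay inside one period. The precision that the article credits to the cross-over therefore has no counterpart in the tests it names.

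The second difficulty is that there are two answers. Group A minus group B estimates the flour effect at week 8 and minus the flour effect at week 16. Once the sign is aligned, the two estimates are negatively correlated, because a chance imbalance between the groups raises one and lowers the other. The article neither ranks nor combines them. If one is significant and the other is not, the conclusion is undefined and could be chosen after the results are seen.

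**Working it through.** **Inputs from the protocol article.** 40 evaluable women, taken here as 20 per sequence; effect 3.1 µg/dL; two-sided 5%; power 90%. "The target was to recruit 50 households (50 eligible women) to be able to accommodate a 20% attrition rate": 40/(1 − 0.20) = 50, which reproduces.

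**Inputs not in the article (assumptions).** Between-woman SD *s* at each period end, within-woman correlation *r* between period ends (range 0 to 0.8), no carry-over, normal data.

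**Step 1. What the sample size implies.** With z = 1.960 + 1.282 = 3.242:

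- Within-woman reading: SD of differences = 3.1 × √40 / 3.242 = 6.05, or 5.90 with the t distribution.
- Two-group reading (20 against 20): SD = 3.1 / (3.242 × √(2/20)) = 3.02, or 2.95 with the t distribution.

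The article gives no SD that would decide between them, so both are carried forward.

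**Step 2. Standard errors.** With N = 40:

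- Single-week group difference: variance 4*s*²/N.
- Cross-over contrast: variance 2*s*²(1 − *r*)/N.
- SE ratio: √(2/(1 − *r*)), which is 2.0 at *r* = 0.5 and 3.2 at *r* = 0.8.
- Single-week difference adjusted for a baseline that also has correlation *r*: variance 4*s*²(1 − *r*²)/N. The SE ratio becomes √(2(1 + *r*)), which is 1.73 at *r* = 0.5 and 1.90 at *r* = 0.8.

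**Step 3. Within-woman reading.** *s* = 5.9/√(2(1 − *r*)). The cross-over SE is 5.9/√40 = 0.93 and its power is 90%. At *r* = 0.5, *s* = 5.9 and the weekly SE is 5.9 × √(2/20) = 1.87. At *r* = 0.8, *s* = 9.33 and the weekly SE is 2.95. Power is from the noncentral t; the last two columns are from simulated trials in which the 3.1 µg/dL effect is real.

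| *r* | One weekly test | Same, baseline-adjusted | Cross-over contrast | Exactly one week significant | Both significant |
|---|---|---|---|---|---|
| 0.5 | 37% | 46% | 90% | 59% | 7% |
| 0.7 | 24% | 42% | 90% | 46% | 1% |
| 0.8 | 18% | 40% | 90% | 35% | 0.3% |

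Even at *r* = 0 a weekly test has 63% power.

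**Step 4. Two-group reading.** *s* = 2.95, so the weekly SE is 2.95 × √(2/20) = 0.93 and each weekly test has 90% power. Both are significant in about 80% of trials and exactly one in about 20%. The cross-over SE at *r* = 0.5 is 2.95 × √(2 × 0.5/40) = 0.47, and its power is nearly 100%.

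**Step 5. False positives.** If either week may be read as the answer, two 5% tests give at least one false positive with probability 1 − 0.95² = 9.75% if independent. With the negative correlation, simulation gives 9.6% at *r* = 0.3 and 8.4% at *r* = 0.7. This does not depend on how the sample size was derived.

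**The case against.** A reader might infer that the plan discards the cross-over altogether. The article does not support that. It plans a mixed model for repeated measurements on the same woman, which is the usual vehicle for within-woman information. That flour, period and sequence terms are not listed is no fault in a condensed article whose full plan is not shown. What remains is narrower: the model is assigned to adjusted analyses and not made primary, while the simple weekly tests are attached to the primary question.

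A reader might also infer that the power claimed for the cross-over is definitely lost. That follows only if 40 was a within-woman calculation. On the two-group reading each weekly test has the stated 90%. On the within-woman reading too, the unadjusted test is the harshest benchmark: baseline adjustment lifts power from 18–37% to 40–46%, which is still well short of 90%.

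The week-8 comparison is a valid randomised contrast, free of carry-over. Carry-over could weaken week 16, but that sample follows eight weeks on the second flour, and no figure in the article supports any particular residual. Carry-over would also bias a pooled cross-over estimate, so it does not by itself favour the remedy.

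None of this removes the absence of a rule for choosing between the two results.

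**Conclusion.** The point holds in this form: the tests named for the primary question do not use the within-woman contrast on which the article relies for power, and they give two results without saying which decides. The lack of a deciding rule holds whatever the SD and correlation.

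The size of the loss is conditional. If 40 was a within-woman calculation, each weekly test has 18–37% power unadjusted, or 40–46% baseline-adjusted, for *r* between 0.5 and 0.8, against 90% for the cross-over contrast; the unadjusted tests disagree in about 35–59% of trials. If it was a two-group calculation, weekly power is 90% and disagreement about 20%, with the cross-over contrast close to 100%. The correlation, the equal correlation with baseline and the absence of carry-over are assumptions. On either reading the cross-over contrast is the more powerful analysis and gives a single answer.

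**What to change.** Name one primary estimate: the biofortified-minus-control flour effect from the mixed model already planned, fitted to end-of-period plasma zinc (weeks 8 and 16), with flour, period and sequence as fixed effects and woman as a random effect, reported with a 95% CI. Report the baseline-adjusted week-8 group comparison as a carry-over-free sensitivity analysis. Label the separate weekly t or Mann-Whitney tests, and the week 4 and week 12 results, as supportive. State how the sample size of 40 was derived, with its SD and whether it was paired or two-group.

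The cost is wording. No new data are needed, the article describes plasma samples as still to be shipped for analysis, and the data analysts are blind to the order of flours. The downside is that, with a direct switch and no washout stated, the pooled effect assumes limited carry-over. The week-8 analysis checks this only weakly (about 40–46% power for the flour effect itself on the within-woman reading), and in a two-period design the sequence term is confounded with carry-over. The assumption should therefore be stated openly and not treated as tested.
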